**Methods:**

A randomized, controlled clinical trial in 58 women with post-mastectomy lymphoedema. The control group includes 29 patients with standard treatment (skin care, exercise and compression measures, bandages for one month and, subsequently, compression garnments). The experimental group includes 29 patients with standard treatment plus Manual Lymphatic Drainage. The therapy will be administered daily for four weeks and the patient's condition will be assessed one, three and six months after treatment.

The primary outcome parameter is volume reduction of the affected arm after treatment, expressed as a percentage. Secondary outcome parameters include: duration of lymphoedema reduction and improvement of the concomitant symptomatology (degree of pain, sensation of swelling and functional limitation in the affected extremity, subjective feeling of being physically less atractive and less feminine, difficulty looking at oneself naked and dissatisfaction with the corporal image).

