Manual Lymph Drainage (MLD) is a massage technique that involves the skin surface only and follows the anatomic lymphatic pathways of the body. A session of manual lymph drainage starts centrally in the neck and trunk to clear out the main lymphatic pathways, thereby facilitating drainage from the arm. Unlike other types of massage, it produces neither blush nor pain and it does not even have a stimulant effect. To successfully complete this technique, a knowledge of the anatomical distribution of the lymphatic and superficial ganglions and of their interconnections is necessary. The MLD is carried out in a descending manner to facilitate the flow of the lymph from the affected areas to those not affected. It is possible to carry out MLD in the case of late or latent lymphoedema three days postsurgery if contraindications do not exist. There are several schools (Vodder, Leduc, Foldie), but they all agree on the fundamental aspects. The MLD must be applied by a physical therapist trained for it. Its application demands a long period of time (from 45 to 60 min.) and it is usually performed once a day (four or five times a week) for 2 to 4 weeks. A study carried out by Leduc and Colls demonstrated that the greatest reduction of the oedema is obtained in the first week of treatment; during the second week the results became stable [15].

The results from several case studies (including over 400 patients) clearly showed that treatment with MLD and compression bandaging had a volume-reducing effect. However, the interpretation of these results is limited due to the methodology used, and their design did not offer the possibility to investigate the extent to which MLD treatment contributed to the reduction of lymphoedema.

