#### Secondary Outcomes

The results of the Spanish validated quality of life questionnaires, EORTC QLQ-C30 version 2.0 for cancer in general and EORTC QLQ-BR23 specific for breast cancer, are used to assess the efficacy of the treatment, measuring the improvement of the lymphoedema concomitant symptomatology. Particularly, the items of the latter referring to the upper extremity (47, 48, 49) and to the corporal image (39, 40, 41, 42) are analyzed and the higher the score, the worse the result.

The secondary outcomes include:

• Degree of pain in the affected upper extremity

• Degree of sensation of swelling in the affected upper extremity

• Degree of functional limitation in this extremity

• Subjective feeling of being physically less atractive

• Subjective feeling of being less feminine

• Difficulty looking at oneself naked

• Dissatisfaction with the corporal image

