### Interventions and distribution of tasks

The rehabilitation physician's functions include:

1. Selection call: the physician determines whether the patient meets inclusion criteria and if so, she is randomized into a treatment group. He/she carries out a complete medical history (history and complete physical exam, taking measurements of both upper extremities for the calculation of lymphoedema volume). He/she explains and provides the informed consent and collects the signed copy. He/she gives the quality of life questionnaire to the patient, who will complete it before starting the outpatient treatment.

2. Week 2 of treatment: Examine the patient. Take measurements of the upper extremities. Rule out the existence of treatment-related side effects. Make the request for a lymphoedema garment. Collect the quality of life questionnaires.

3. Week 5 of treatment: Examine the patient. Take measurements of the upper extremities. Rule out the existence of treatment-related side effects. Check the sleeve. Give a compliance diary to the patient.

4. Week 12 of treatment: To examine Explore the patient. Ask about possible complications that may lead to withdrawal from the study. Take measurements of both upper extremities. If the response to the treatment is good, the patient will be encouraged to continue complying with treatment. The patient's diary is reviewed. A second quality of life questionnaire is provided. The treatment is continued at home. If the response to the treatment is poor, the patient is included again in an outpatient treatment for a month so that if the patient has previously received TH now he/she would be treated with TH + DL and if he/she has been previously treated with TH + DL now she would be treated with DL. The patient is examined at week 16. Measurements of the upper extremities are taken. The presence of treatment-related side effects is ruled out.

5. Week 18 of treatment: the patient is examined. Measurements of the upper extremities are taken. The presence of treatment-related side effects is ruled out. The sleeve is reviewed. A second quality of life questionnaire is delivered.

6. Final call: Week 24 of treatment: the patient is examined. The patient is asked about possible complications that may lead to withdrawal from the study. Measures are taken in both upper limbs. The sleeve is reviewed.

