At the end of the study, the patient's calendar is collected. The completed Quality of Life questionnaire is collected. Collaboration with the statistics department is carried out for data completion and publication.

The Physiotherapist's tasks include

1. She/he phones the patients of the study and notifies them of the starting of the treatment. She/he randomizes the patients in treatment A or B according to the instructions of the Biomedical Research Foundation.

2. She/he applies the prescribed treatment and instructs patients in the proper execution of exercise and care of the affected limb.

3. She/he makes the appointment with the patients for review in consultation.

4. She/he notifies the physician of any incidents that may occur.

Finally, the BIOMEDICAL RESEARCH FOUNDATION (BRF) randomizes the patients in the two different treatment groups, monitors the study and facilitates statistical analysis of the data and results.

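### The baseline quality-of-life form is due before treatment but is collected only at the week-2 visit, too late to correct one that is blank, incomplete or late

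*Protocol article*

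**What the plan says.** The handling of the form is set out in the protocol article under Interventions and distribution of tasks.

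- Item 1, selection call, on the physician: "He/she gives the quality of life questionnaire to the patient, who will complete it before starting the outpatient treatment". In the same item the physician takes back the signed consent. No return of the questionnaire is mentioned there.
- Physiotherapist's tasks, item 1: "She/he phones the patients of the study and notifies them of the starting of the treatment". Treatment therefore starts at some later date. The interval is not given.
- Item 2, week 2 of treatment: "Make the request for a lymphoedema garment. Collect the quality of life questionnaires". This is the first collection step named.
- Item 4, week 12: "A second quality of life questionnaire is provided".
- End of study: "The completed Quality of Life questionnaire is collected".

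The Abstract (Methods) describes the intensity of treatment: "The therapy will be administered daily for four weeks and the patient's condition will be assessed one, three and six months after treatment". Secondary Outcomes says that the questionnaires serve for "measuring the improvement of the lymphoedema concomitant symptomatology" and lists seven symptom and body-image outcomes.

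**The concern.** A baseline form has to be in hand, or at least verified, while it can still be corrected. Here the named collection point falls inside the four weeks of daily treatment. If a woman forgot the form, lost it or left items blank, this is discovered at week 2, when anything she then fills in describes her state under treatment. With no completion date required, such a form would look like any other baseline at analysis.

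At stake are the symptom outcomes, not the primary outcome. Limb volume is measured by the physician at the selection call and does not depend on this form. The symptom outcomes still matter: the Background leaves open whether manual lymphatic drainage can relieve symptoms even where volume does not improve, and the questionnaires are the instrument for answering that.

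**Working it through.** The plan states no figure on this point, so there is none to reproduce. The check has two parts.

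**1. Which form is collected at week 2?**
One questionnaire is handed out before week 2, at the selection call. None is handed out at week 2 or week 5. The one provided at week 12 is called the second. The form collected at week 2 is therefore the baseline form. The week-5 visit appears to follow the four treatment weeks. By the same counting the week-2 visit follows about one week of treatment, and at most two. On either count treatment has begun.

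**2. What would a late form do?**
Notation:
- e_A and e_B: true mean symptom improvement in the control and experimental arms, with D = e_B − e_A.
- p: share of baseline forms completed late, assumed equal in both arms.
- f: fraction of the eventual effect already present when a late form is completed, from 0 to 1.
- β: weight given to baseline in the analysis. β = 1 is a change score, β = 0 is follow-up scores only, and baseline adjustment normally lies between.

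On a scale where higher is worse, late forms lower the mean recorded baseline in arm g by p·f·e_g. The recorded baselines then differ between arms (B − A) by −p·f·D, and the follow-up scores differ by −D. The estimated contrast is

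−D − β(−p·f·D) = −D(1 − β·p·f).

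The proportional loss of contrast is thus β·p·f. None of the three quantities is in the document. Taking p as 10%, 20% or 30%, purely as assumptions:

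| p | β = 0 (follow-up only) | β = 1, f from 0 to 1 |
|---|---|---|
| 10% | 0 | 0 to 10% |
| 20% | 0 | 0 to 20% |
| 30% | 0 | 0 to 30% |

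If the late share differs by arm, the change-score contrast becomes e_B(1 − p_B·f) − e_A(1 − p_A·f). This exceeds D when p_A·e_A is larger than p_B·e_B, so even the direction is not guaranteed.

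**What is known about f?**
The Background cites a study in which "the greatest reduction of the oedema is obtained in the first week of treatment; during the second week the results became stable". That concerns oedema. It does not time pain, function or body image, so it makes f above 0 plausible but does not set its value.

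**The case against.** The strongest reply is that the protocol fixes the baseline correctly. The patient is told to complete the form before treatment, and the date of collection is not the date of completion. A form filled in on time and handed over at week 2 is a valid baseline. Dating, checking for blanks and retrieving forms are also details that an article may leave to the full protocol.

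The first part stands: a reader might infer that the baseline is in effect a week-2 measurement, and the text does not say so. The second part stands only in part. The article's silence on checks is no finding, but it does name a collection time, and that time is a poor choice whatever the full protocol adds.

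Other stronger readings are tempting and are not supported:

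- **The form goes home with the patient.** The later phone call about the start date makes this likely, but it is not stated.
- **The baseline is lost for anyone who leaves before week 2.** Nothing says that a completed form is not retrieved. Moreover, the next questionnaire is at week 12, so a woman who leaves the study before week 2 has no follow-up score, with or without a baseline. Applying the plan's 30% dropout evenly over 24 weeks gives 58 × 0.30 × 2/24 = 1.45 such women, or 58 × 0.30 × 1/24 = 0.73 if week 2 follows one week. The document gives no timing of dropout, and either way the loss comes from the missing outcome. The promise to analyse all patients is not broken by form collection.
- **All seven outcomes are change scores.** Improvement appears in the sentence introducing them. The listed items are degrees and feelings, and Statistical methods speaks of differences between groups without specifying change from baseline.
- **The contrast shrinks by 10% to 30%.** Those are the upper ends of assumed cases (β = 1, f = 1), not estimates.

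**Conclusion.** The point holds in a limited form. The baseline form is due before treatment, its only named collection is at week 2 of daily treatment, and no dating step is stated. A defective or late form is therefore found when it can no longer serve as a pre-treatment value, and a late one may not be recognised at all.

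The effect on results is conditional. It arises only if some forms are late, if symptoms have already responded by then, and if the analysis uses baseline. With equal late shares in the two arms it pulls the contrast towards zero by the fraction β·p·f, which cannot be evaluated from the document. Blank forms cost baseline data rather than adding bias of this kind. Early leavers are not a material part of the problem. Only secondary outcomes are touched, but a missed baseline cannot be recreated and prevention is nearly free, so the change is worth making.

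**What to change.** Under Interventions and distribution of tasks:

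1. Remove collection of the baseline questionnaire from the week-2 visit.
2. Add to the physiotherapist's tasks that at the first outpatient session, before the first treatment, the form is handed in, dated and checked for blanks. A missing or incomplete form is completed there and then.
3. State that any form dated after the start of treatment is flagged and is not treated as a pre-treatment baseline.

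The cost is a line or two in the task list and a few minutes at a session the patient already attends. No visit is added and treatment is unchanged.

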The third published randomized trial, involving 42 women with modest stage I or II lymphoedema compared standard therapy alone with standard therapy plus MLD and training in self-massage (level I evidence). Standard therapy included the use of a custom-made sleeve-and-glove compression garment worn during the day, instruction in physical exercises, education in skin care, and information and recommendations about lymphoedema. Both groups obtained a significant reduction in limb volume, a decrease in discomfort and increased joint mobility over time. However, no significant differences in objective measures regarding change in arm volume or subjective measures of symptoms related to lymphoedema were found between the 2 groups [18]. This study investigated the effect of eight sessions of MLD over two weeks, so the MLD course was relatively short and the study group was limited to those with mild to moderate swelling (20-30% of difference). Information about quality of life was gathered using the questionnaire EORT QLQ-C30, but the results were not considered in the final evaluation. On the other hand, there is no evidence that shows that the effect of MLD is permanent - because previous studies measured the volume directly after the conclusion of MLD - or if the MLD can be effective in decreasing the symptoms, in spite of not obtaining an improvement in volume reduction. Therefore, the utility of MLD as part of the Physical Complex Therapy has turn out to be relevant, given the exclusive dedication of the therapist that it entails and the extra cost in relation to the potential health benefits for patients.

The aim of this study is to analyze the short-term and long-term effectiveness of Manual Lymphatic Drainage (MLD) in the treatment of postmastectomy lymphoedema in order to reduce the volume of lymphoedema and evaluate the improvement of the concomitant symptomatology.

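### No quality-of-life questionnaire is scheduled at the week-5 visit, so the seven symptom outcomes have no end-of-treatment value

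*Protocol article*

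**What the plan says.** The last paragraph of the Background states the aim: "The aim of this study is to analyze the short-term and long-term effectiveness of Manual Lymphatic Drainage (MLD) in the treatment of postmastectomy lymphoedema". The same sentence goes on to name both volume reduction and relief of the accompanying symptoms. The abstract's Methods section gives the timing: "The therapy will be administered daily for four weeks and the patient's condition will be assessed one, three and six months after treatment".

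Under Secondary Outcomes, the symptom outcomes are taken from the QLQ-BR23: "the items of the latter referring to the upper extremity (47, 48, 49) and to the corporal image (39, 40, 41, 42) are analyzed". Seven outcomes are then listed.

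The section on interventions and distribution of tasks sets out what happens at each visit:

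- At selection the patient receives the questionnaire and is to fill it in before outpatient treatment begins.
- At week 2: "Make the request for a lymphoedema garment. Collect the quality of life questionnaires".
- At week 5: "Week 5 of treatment: Examine the patient. Take measurements of the upper extremities". Side effects, the sleeve and a compliance diary follow. No questionnaire is listed.
- At week 12: "The patient's diary is reviewed. A second quality of life questionnaire is provided".
- At week 18: "A second quality of life questionnaire is delivered".
- At week 24 no questionnaire is handed out. The text that follows says a completed one is collected at the end of the study.

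**The concern.** The trial sets itself a short-term question and a long-term one, each for volume and for symptoms. Volume has a measurement at the end of the four-week course. Symptoms do not, because they are captured only by the questionnaire and none is due at that visit.

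This bears on a question that the Background raises itself: whether MLD may relieve symptoms even where it does not reduce volume further. To look at that at the end of treatment, symptoms and volume must be measured together. As scheduled, only volume is available then.

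The first later form falls at the visit where poor responders are moved to the other regimen. If it is completed after that move, the scores of those patients no longer reflect the randomised treatment alone.

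**Working it through.** The plan gives no figure for this point, so the check sets the schedule against the aim. Weeks are counted from the start of treatment, as the task list does.

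**Source of the outcomes.** Items 47, 48 and 49 are 3 items and items 39 to 42 are 4. 3 + 4 = 7, which matches the seven symptom outcomes listed. None of them has another stated source.

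**Schedule, visit by visit.**

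| Visit | Arm measurements | Questionnaire |
|---|---|---|
| Selection | yes | given, to be completed before treatment |
| Week 2 | yes | collected |
| Week 5 | yes | none listed |
| Week 12 | yes | second form provided |
| Week 16 (re-treated patients) | yes | none listed |
| Week 18 | yes | second form delivered |
| Week 24 / end of study | yes | none issued; a completed form collected |

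**Size of the gap.** The MLD course lasts four weeks. From its end to the first post-baseline form is 12 − 4 = 8 weeks. From the week-5 visit it is 12 − 5 = 7 weeks. The number of symptom outcomes with an end-of-treatment value is 0 of 7.

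**Against the abstract.** If one, three and six months are counted from the start of treatment, they correspond to weeks 5, 12 and 24, and the first of these has no questionnaire. If they are counted from the end of the course, one month later is about week 4 + 4 = 8, where no visit is listed at all. Neither reading yields a one-month symptom score.

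**Status of week 12.** The switch of poor responders is decided at this visit. A form completed there beforehand compares the arms as randomised, about 8 weeks after MLD. But the list says only that the form is provided. For the baseline form it does say when completion is due. The next collection named is at the end of the study, unless the week-18 entry means that the week-12 form is handed back then. In that case completion could fall anywhere in 18 − 12 = 6 weeks, a period that includes the month of re-treatment.

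**Later forms.** Two visits name a second form. The form collected at the end is either the week-18 form or one whose issue is not listed. The number of forms per patient cannot be settled from the text.

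**The case against.** The strongest points on the other side are these.

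- *Later assessment may be deliberate.* The Background criticises earlier trials for measuring volume straight after MLD, and the article never defines short-term. A week-12 comparison is a legitimate answer to whether symptom relief persists. This stands. It explains a week-12 form but not the absence of one at week 5, since the aim names both horizons.
- *The abstract does not promise a one-month questionnaire.* It says that "the patient's condition will be assessed one, three and six months after treatment", and the only outcome explicitly tied to the first month is volume, which week 5 delivers. This also stands: the abstract alone does not prove a contradiction. If the patient's condition includes symptoms, the two sections must be reconciled.
- *The numbering is unreliable.* Since week 18 also speaks of a second form, the label at week 12 is weak proof that nothing came before it. The week-12 sentence also sits between the instructions for good and for poor responders, so it might apply to good responders only, with week 18 for the others. The text does not settle this. Either way the week-5 list contains no form, and on the second reading there would not even be a common week-12 comparison.
- *The article is condensed.* The full protocol may contain more. But the article does not merely omit detail here: it lists the week-5 tasks one by one.

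A reader might also infer that baseline scores are contaminated because forms are collected at week 2. The documents do not support this. Completion is specified as before treatment, and week 2 is only when the forms are gathered.

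**Conclusion.** The point holds as a gap in the timing of secondary outcomes. Run as written, the trial has no end-of-treatment value for any of its seven symptom outcomes, and the first post-baseline form comes about 8 weeks after MLD ends. This rests on taking the week-5 task list as complete and on counting weeks from the start of treatment.

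A reader might go further and infer that the trial cannot say whether MLD relieves symptoms. That is too strong. A week-12 form completed before any change of regimen gives a randomised comparison of persisting effect. Nor does the article give any time course for symptoms from which to argue that week 5 is when an effect is most likely to show; the study it cites on early response concerns oedema. What is lost is the short-term comparison, and what is at risk is the week-12 one, because its completion time is not fixed.

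The primary outcome and the sample size are untouched. The change is worth making because it serves the stated aim at almost no cost.

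**What to change.** 1. Give and collect the QLQ-BR23, at least items 39-42 and 47-49, at the existing week-5 visit, alongside the arm measurements. It need not become the main symptom time point.
2. State that the week-12 form is completed and handed in at that visit by every patient, before response is judged.
3. Reconcile the later forms: how many there are, at which visit each is issued and collected, and a distinct number for each. Say whether the form collected at the end is the week-18 form or a separate one.
4. Make the assessment times in the abstract agree with the visit list, including whether months are counted from the start or the end of treatment. If short-term symptom relief is not intended as a question, the aim should say so.

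The cost is one more short self-completed form per patient, at most 58 in all (58 patients × 1 form), with no new visit and no change in sample size. The other items are changes of wording.

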### Treatment groups

#### Group A or Control Group

Ambulatory treatment is performed for one month. Specific exercises and prevention measures are taught. In the first four weeks, multilayer bandage is applied daily. Bandaging consists of a first layer of cotton (Velband) followed by protection at the points of support and a bandage of low elasticity (Comprilan) of different widths (six centimeters for the area of the hand and eight centimeters for the rest of the extremity).

The tailor-made sleeve for lymphoedema with a gauntlet without protection at the edges and with extension to the shoulder is applied for the first four weeks of treatment. The sleeve is used all day, and at night interruption is allowed. Later on, the patient will continue domiciliary treatment, performing specific exercises for 30 minutes twice a day without experiencing fatigue, and wearing the lymphoedema sleeve for at least 12 hours.

If after three months of treatment a satisfactory response is not achieved, an ambulatory treatment will be re-established for one month, and this time the experimental treatment (group B) will be used.

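### The visit schedule does not secure a symptom questionnaire from every patient before poor responders change treatment at week 12

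*Protocol article*

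**What the plan says.** The Secondary Outcomes section lists seven outcomes (pain, swelling, functional limitation and four body-image items) and assesses them with the two EORTC questionnaires. It gives no assessment times. The timing comes from the section Interventions and distribution of tasks:

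- **Selection:** "He/she gives the quality of life questionnaire to the patient, who will complete it before starting the outpatient treatment".
- **Week 2:** "Collect the quality of life questionnaires".
- **Week 5:** no questionnaire is mentioned.
- **Week 12:** the arms are measured, good responders are encouraged to continue and the diary is reviewed. Then: "A second quality of life questionnaire is provided. The treatment is continued at home. If the response to the treatment is poor". The last of these sentences reads on: "If the response to the treatment is poor, the patient is included again in an outpatient treatment for a month".
- **Week 16 (switched patients):** examination, measurement and side effects, but no questionnaire.
- **Week 18:** "The sleeve is reviewed. A second quality of life questionnaire is delivered".
- **Week 24 and end of study:** "The completed Quality of Life questionnaire is collected".

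The Group A section says of controls without a satisfactory response at three months that "this time the experimental treatment (group B) will be used". The Group B section contains a mirror-image rule for the experimental arm.

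**The concern.** Up to week 12 the arms are meant to differ only by Manual Lymphatic Drainage (MLD). After that, patients judged poor responders receive further treatment under a rule that crosses the arms. A symptom comparison that reflects the randomised treatments alone therefore has to be made by the week-12 visit, in all patients and before anyone changes treatment. The schedule has one form that could serve, and it does not say who receives it, when it is completed or when it is returned.

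Improvement in symptoms is part of the stated aim. If controls switched to MLD answer during or after that course, their answers describe symptoms under MLD, and a true benefit would be diluted. If poor responders have no form at this point, the comparison is between subgroups defined by outcome. No later analysis can recover a pre-switch answer that was never collected or dated.

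**Working it through.** The point rests on the order of the scheduled steps. The plan states no expected share of switched patients, so it has no figure of its own to reproduce here.

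**Step 1. Handing out, completion and collection compared.**

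| Form | Handed out | Completion time stated | Collection stated |
|---|---|---|---|
| Baseline | Selection visit | Yes, before outpatient treatment | Week 2 |
| Called second | Week 12 | No | None at week 12 or 16 |
| Also called second | Week 18 | No | None separately stated |
| One completed form | – | – | End of study (week 24) |

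The schedule treats handing out and collecting as separate acts, and it fixes completion only for baseline. With no form at week 5, the week-12 form is the only post-baseline one that could precede the switch.

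**Step 2. Two readings of the week-12 sentence.**

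- *Reading A: everyone receives the form.* The switched month runs from week 12 to week 16. The next explicit collection is at week 24, which leaves 24 − 12 = 12 weeks for completion. If the week-18 wording means that a form is handed in, 18 − 12 = 6 weeks remain. Both windows contain the whole switched month.
- *Reading B: the sentence belongs to the good-response branch.* It stands between the instruction for good responders and the statement about continuing at home, which cannot apply to patients returning to outpatient treatment. Poor responders would then receive their first post-baseline form at week 18, which is 18 − 16 = 2 weeks after the switched month, and would have none before it.

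**Step 3. Scale, as an illustration.** Inputs from Sample Size: mean reduction 5% (control) and 25% (experimental), SD 25%, 29 patients per arm. Input from Primary Outcome: a good response is a reduction of at least 20%. Assumptions added here: a normal distribution, the same means at week 12, and the 20% cut-off as the trigger for the switch.

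Share below the cut-off = Φ((20 − mean)/25):

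- Control: Φ((20 − 5)/25) = Φ(0.6) = 0.726, and 0.726 × 29 = 21.0 patients.
- MLD arm: Φ((20 − 25)/25) = Φ(−0.2) = 0.421, and 0.421 × 29 = 12.2 patients.

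With the 20 per arm on which the sample size was computed before dropout, the numbers are 14.5 and 8.4.

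Under reading A, these are the patients whose form could be answered after the switch begins. Under reading B, week-12 forms would exist for about 29 − 21.0 = 8.0 controls and 29 − 12.2 = 16.8 MLD patients, selected by their volume response.

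The amount of dilution cannot be computed. The documents give neither a rate of late completion nor an expected effect on symptoms.

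**The case against.** The strongest reply is that late completion is inferred from silence. This is a condensed article, the section is a list of tasks by role, and the moment a form is picked up is often left to a fuller document. The singular form collected at study end could mean that only the last one was still outstanding. No month-3 questionnaire contrast is named as an analysis. The good-response reading would also mean that no switched patient holds a week-12 form at all.

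Part of this stands. The text does not say that forms will be answered late, only that nothing prevents it. But the article itself sets out the questionnaire steps visit by visit, fixes completion for one form and leaves it open for the form that matters most. The good-response reading does not rescue the schedule, because it replaces a form open to late completion with one that is missing for poor responders.

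A reader might infer more than the documents support:

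- **That about 33 of 58 week-12 forms (21 + 12) would be compromised.** That sum counts patients who may switch under the illustrative assumptions. It is not a count of late forms.
- **That the difference is pulled towards zero from both arms.** Dilution is clearest for controls switched to MLD. For switched MLD patients, the Group B section and the week-12 item describe the further treatment differently, so the direction is not established.
- **That the baseline form is also at fault because it is collected at week 2.** Its completion before treatment is already required, so the later pick-up is logistics.

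**Conclusion.** The concern holds in this form: the schedule does not secure a symptom assessment in all patients before the week-12 switch. On either reading of the week-12 sentence, the randomised pre-switch comparison of the seven secondary outcomes is unprotected. It would be safe only if every patient completed the form in clinic at week 12 before any change of treatment, which the article does not say.

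The potential reach is large if the sample-size assumptions, normality and the 20% cut-off apply at week 12: about 73% of controls and 42% of the MLD arm could be candidates for switching. The actual bias is unknown. The primary volume outcome is not affected by this point. The schedule should be corrected because a stated aim depends on these forms and the correction is cheap.

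**What to change.** In Interventions and distribution of tasks:

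1. State that every patient, whatever her response, completes, dates and returns the questionnaire at the week-12 visit before any change of treatment, preferably before she is told her response.
2. State that the final form is completed at the week-24 visit.
3. Number the forms distinctly in place of the two called second, and say whether the week-18 form is a separate assessment.
4. Count as pre-switch only forms dated at or before the week-12 decision.

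The cost is a change of wording and a few more minutes in clinic. No new visit or instrument is needed. This protects the pre-switch comparison only; it does not remove the effect of the switch on later forms. Separately, the Group B section and the week-12 item must be reconciled on what switched MLD patients receive.
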